## Abstract

**Introduction:**

Hospitalised older patients frequently suffer from inadequate sleep, which can lead to patient distress and delayed recovery from acute illness or surgical procedure. Currently, no evidence-based treatments exist for sleeping problems in hospitalised older patients. Benzodiazepines, such as temazepam, are regularly prescribed by physicians, although they have serious side effects; for older patients in particular. Melatonin is proposed as a safe alternative for sleeping problems in hospitalised older patients, but the efficacy of melatonin is unclear in this population. Therefore, the aim of this study is to investigate the effects of melatonin and temazepam compared with placebo on sleep quality among hospitalised older patients with sleeping problems.

**Methods and analysis:**

This study is a multicentre, randomised, placebo-controlled trial. A total of 663 patients will be randomised in a 1:1:1 fashion to receive either melatonin (n=221), temazepam (n=221) or placebo (n=221). The study population consists of hospitalised patients aged 60 years and older, with new or aggravated sleeping problems for which an intervention is needed. The primary outcome is sleep quality measured with the Leeds Sleep Evaluation Questionnaire (LSEQ). Secondary outcomes include sleep parameters measured with actigraphy and medication-related adverse effects.

**Ethics and dissemination:**

This study was approved by the Medical Ethics Committee of the Academic Medical Centre Amsterdam, (No 2015_302). Study findings will be disseminated through presentations at professional and scientific conferences and publications in peer-reviewed journals.

**Trial registration number:**

NTR6908; Pre-results.

Strengths and limitations of this studyThe results of this study will provide knowledge relevant for clinical practice and fill gaps in current guidelines concerning sleep problems in hospitalised older patients.To optimise the generalisability of the findings, this is a multicentre study with participants from different wards and minimal exclusions criteria.This study investigates, next to the effects, also the adverse events of melatonin and temazepam compared with placebo.Patients with cognitive impairment are excluded due to ethical considerations, even though these vulnerable patients may benefit the most from the study outcomes.

## Introduction

### Background

Hospitalised older patients frequently experience sleeping problems due to medical, psychological or environmental disturbances. The prevalence of sleep problems among older patients in medical and surgical wards varies between 30% and 65%.^1–3^ Apart from the feeling of tiredness, insufficient sleep has substantial consequences for hospitalised patients. This includes delayed recovery from acute illness or surgical procedures because of its immunosuppressive effect,^4 5^ risk of delirium and falls^6–9^ and disturbances in metabolic and endocrine functioning.^10 11^

Thus, adequate treatment of sleeping problems is necessary. Today, it is still unclear how sleeping problems should be treated in the hospital. Non-pharmacological interventions are advised as first choice therapy in hospitalised patients,^12–14^ but there is limited evidence to support the effectiveness of non-pharmacological interventions.^15^ With regard to pharmacological interventions, there is insufficient evidence to support its effectiveness for improving quality or quantity of sleep in hospitalised patients suffering from poor sleep.^16^

Currently, up to 29% of older hospitalised patients with sleeping problems receive benzodiazepines,^17 18^ despite a recent meta-analysis of risks and benefits for short-term treatment of insomnia, which stated that benzodiazepines have little effect and may not outweigh the risks of adverse events, especially in a high-risk older population.^19^ Older patients have a higher risk of adverse drug events from benzodiazepines due to altered pharmacokinetics and pharmacodynamics. Common adverse drug events include in-hospital falls, delirium, aspiration and respiratory depression.^20 21^ Furthermore, use of benzodiazepine during hospitalisation can lead to prolonged use at home, which might promote chronic use and substance-dependency.^22^

The neuroendocrine hormone melatonin has been proposed as a safer alternative to improve sleep quality because of its limited side effects.^8 23–25^ Melatonin, produced by the pineal gland at night, is well known to influence circadian rhythm and sleep.^26^ Two randomised control trials (RCTs) investigated the effectiveness of melatonin compared with placebo in older community dwelling persons with chronic insomnia and found that melatonin improved sleep quality significantly.^27 28^ However, studies on the effectiveness of melatonin for sleeping problems in acute hospitalised older patients are scarce. Three RCTs have been performed in adult patients on the intensive care unit,^29–31^ showing inconsistent results; one out of three reported a positive effect of melatonin.^30^ All three studies were underpowered and none specifically assessed older patients with predefined sleep related problems.

Only one small RCT investigated the effectiveness of melatonin on a general medical ward in adults, which resulted in beneficial effects for melatonin compared with placebo on the sleep onset latency and patient satisfaction.^32^

The overall aim of this study is to establish an evidence-based pharmacological treatment for hospitalised older patients with sleeping problems. In this study, we will first hypothesise that melatonin and temazepam are more effective than placebo on sleep quality among hospitalised older patients with sleeping problems and second melatonin is more effective than temazepam.

### Objectives

The primary objective is to investigate first the effects of melatonin and temazepam compared with placebo among hospitalised older patients on self-reported sleep quality. Second, to investigate if melatonin is more effective than temazepam.

The secondary objectives are to investigate the effects of melatonin, temazepam and placebo on:Other self-reported sleep parameters: getting to sleep, awakening from sleep, behaviour following wakefulness.Objective sleep parameters: reduction in sleep onset latency, sleep efficiency, number and duration of wake bouts, time awake after sleep onset.Adverse events related to study medication: incidence of delirium, cognition, number of falls, complications.Length of hospital stay in days.Time needed to reach improvement in self-reported sleep quality.Proportion of good nights of sleep during study period.

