### Intervention

After randomisation, all participants receive the allocated medication once daily which is in the evening before sleep (ante noctem). Study medication will be administered orally starting on the day of study enrolment.

Melatonin 1 mg and temazepam 10 mg will be used as study medication. The dosage of 1 mg melatonin is chosen based on a recent systematic review, to best mimic the normal physiological circadian rhythm of melatonin by avoiding prolonged supra-physiological blood levels in case of higher dosages.^35^ The dosage of 10 mg temazepam is the recommend dose for older patients.^36^

Study medication will be continued to either a maximum of 10 days, or 12 hours before hospital discharge, or after three consecutive nights of good sleep, or until participant decides to withdraw from the study. In case sleep problems do not resolve with study medication, the dosage can be doubled. This decision will be left to the patient’s attending physician. Attending physicians are instructed only to consider a double dose when the patient has slept badly for two nights in a row, in case there are no environmental or treatable physical factors that could cause the poor quality of sleep (QOS) and they should take possible adverse effects of study medication into account. Double doses of study medication will be registered in the case report form and in the medical record.

Study medication will be discontinued if a condition occurs that needs treatment with benzodiazepines (eg, anxiety), if events occur that imply a higher risk of adverse events (eg, respiratory insufficiency or starting chinolones) and in case of persisting sleeping problems. Persisting sleep problems is defined as self-reported poor QOS for three consecutive nights after study medication has been doubled.

After study medication is discontinued, either due to a reason listed above or due to end of study period, treatment will be provided according to the hospital’s protocol and under the responsibility of the attending physician. Patients remain in the study and follow the study protocol, except for using study medication.

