### Timing of measurement and outcome measures

Demographic data, such as age, sex, nationality, highest educational status and living situation will be collected at baseline. Medication use, blood tests 24 hours prior to study inclusion or 24 hours after study inclusion, severity of foregoing sleep problems, depression and anxiety, level of independence, health status and vulnerability (eg, fall risk) are measured at baseline. Primary and secondary outcome measures will be recorded at baseline (T0) and every day until the 10th day (T1–T10) or until discharge. Table 1 provides an overview of the timing of measurements and the outcome measures.

**Table 1 T1:** Overview of the timing of measurements and outcome measures

Measurement	Description and instrument	Timepoints		
		Baseline	Daily	Discharge
Sleep quality	*Leeds Sleep Evaluation Questionnaire (LSEQ)*,^38 44^ 10-item questionnaire, self-rated, on 0–100 mm line. Validated tool for measuring changes in sleep on four domains; getting to sleep, quality of sleep, ease and awakening from sleep and alertness and behaviour following wakefulness The Dutch version of the LSEQ is forwards and backwards translated according to the translation guidelines^45^	x	x	
	Numeric rating scale for overall sleep, an overall numeric rating of quality of sleep. With ‘0’ representing a very bad night’s sleep and ‘10’ representing a very good night’s sleep	x	x	
Sleep pattern	*The core consensus sleep diary* 46, a 10-item sleep log to gain insight in the sleep pattern of a participant	x	x	
Factor influencing sleep	Based on literature,^15 47–50^ an overview is made of 10 influencing factors on sleep in hospitals. Participants can indicate whether these factors influenced their sleep and if so, to what extent	x	x	
Objective sleep parameters	*Actigraphy, MotionWatch 8,* a wristwatch-like device, worn on the non-dominant hand. The actiwatch registers motion in epochs of 30 s. Based on motion sleep latency, sleep efficiency, number and duration of wake bouts, time awake after sleep onset in minutes can be calculated	x	x	
Cognition	*Mini-Mental State Examination* 51, a 10-item screening tool to evaluate global cognitive function	x	x*	
	*Stroop Colour-Word test* 52 53, *consists of three subtasks. Used to measure attention, processing speed, cognitive flexibility and working memory*	x	x*	

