#### Primary outcome

The primary outcome of the study is change in self-reported sleep quality during the treatment period (T0–T10). Sleep quality will be assessed with the Leeds Sleep Evaluation Questionnaire (LSEQ).^37 38^

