#### Secondary outcomes

Change in self-reported sleep measures: getting to sleep, awakening from sleep and behaviour following wakefulness during treatment period will be assessed with the other subscales of the LSEQ. These measures will be assessed on T0 until T10.Objective sleep parameters. To assess objective sleep parameters participants will wear a MotionWatch eight during the study period (T0–T10). This wristwatch-like device will calculate sleep latency, sleep efficiency, number and duration of wake bouts, time awake after sleep onset in minutes based on motion of the patient.Number of good night sleep. Good nights of sleep will be assessed with a numeric rating scale for QOS. On the numeric rating scale ≤4 is considered a bad night’s sleep, 5–6 is neither a good or bad night’s sleep and ≥7 is a good night’s sleep.^39^
Time needed to reach improvement in self-reported sleep quality will be based on the LSEQ as well. Improvement of sleep quality is defined as the first day that an improvement of 10 mm is reached compared with baseline.Adverse events defined as confusion, delirium, reduced consciousness, falls, aspiration and other additional adverse events will be monitored daily on T0–T10.Length of hospital stay in days will be recorded at discharge.

To ensure consistency and optimisation of the data collection process, all members of the research team who will include patients in the study will follow a training how to conduct measurements according to Standard Operating Procedures and how to fill out the Case Report Forms. Non-adherence to the study protocol will be obviated as much as possible. However, when it occurs this will be registered by the research team.

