### Data analysis

Data will be analysed according to an intention-to-treat principle. Researchers are not aware of the allocation of the intervention and therefore analyses will be conducted in a blinded way. A per-protocol analysis will be conducted excluding patients that did not receive the intervention according to protocol and were incorrectly included in the study. To determine the effects of temazepam, melatonin or placebo on sleep quality, linear mixed models will be used. Analysis will be performed on change of sleep quality over time taking baseline value into account (ie, night before start of study medication). The following covariates will be added to the model: age, gender, different concurrent medication (eg, morphine), severity of disease diagnosis (Rotterdam Symptom Checklist (RSCL), pain severity (visual analogue scale, RSCL), acute or elective admission to the hospital, foregoing sleep problems (insomnia severity index), number of patients in the room, level of independency (Katz Index of Independence in Activities of Daily Living), level of anxiety (Hospital Anxiety Depression scale) and days in the hospital before inclusion. Linear mixed models will also be used to evaluate getting to sleep, awakening from sleep, behaviour following wakefulness and the objective sleep parameters measured with actigraphy. Analyses of the time needed to reach improvement of sleep quality will be done with an interval-censored survival analysis. Proportion of good nights of sleep measured with the numeric ratings scale will be analysed, when normally distributed, with multiple linear regression analysis. For the analysis of adverse events related to study medication, descriptive statistics will be used to show which adverse events occurred. Depending on the occurrence of these adverse-events and distribution, log-linear analysis, Poisson or multiple regression analysis will be used. Time to occurrence of an adverse event will be analysed with Cox regression.

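### The window for the good-nights proportion is badly fixed: read with the protocol's own time points, it takes in the untreated baseline night

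*Protocol article*

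**What the plan says.** Four places in the protocol article bear on the window.

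- **Objectives** sets it: "Proportion of good nights of sleep during study period".
- **Secondary outcomes** gives time points for the study period once, in the actigraphy item: "participants will wear a MotionWatch eight during the study period (T0–T10". The good-nights item in the same section names a count rather than a proportion, sets 7 or above as a good night, and gives no time points.
- **Timing of measurement and outcome measures** separates baseline from follow-up; outcomes are "recorded at baseline (T0) and every day until the 10th day (T1–T10) or until discharge". Table 1 marks the numeric rating of sleep both at baseline and daily.
- **Data analysis** says what the baseline night is, for the sleep-quality model: "taking baseline value into account (ie, night before start of study medication". For this outcome it says: "Proportion of good nights of sleep measured with the numeric ratings scale will be analysed, when normally distributed, with multiple linear regression analysis". It gives no denominator and says nothing about T0.

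**The concern.** Taken together, these places put a night on which no capsule had been taken inside the window over which good nights are counted. For the primary outcome the same T0–T10 span does no harm, because T0 is the reference for a change. A proportion has no reference night, so T0 would become an ordinary night in both numerator and denominator.

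That night is not neutral. Patients enter because of new or aggravated sleep problems judged to need drug treatment (Eligibility criteria), so T0 will mostly fail the threshold of 7. Its weight is 1/(n+1), which is largest in short stays. Two things are at stake: the estimated treatment difference would be pulled towards zero, and the score would depend on length of stay, which is itself a secondary outcome.

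**Working it through.** **Inputs from the protocol.** T0 is baseline and T1–T10 are daily. Baseline is the night before study medication. A good night is a rating of 7 or above. Ratings run to day 10 or discharge. There are 210 patients per arm before the dropout allowance. The protocol gives no figure for this outcome, so there is none to reproduce.

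**Inputs that are assumed.** The smallest n is taken as about 2, inferred from the exclusion of patients expected to stay less than 48 hours. That is an expectation, so n=1 can occur. The rates of good nights and the lengths of stay used below are also assumptions.

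**Step 1: shrinkage if T0 is counted.** Let a patient have g good nights among n post-baseline nights, and let b be 1 if T0 was good and 0 if not.

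- Score without T0: g/n. Score with T0: (g + b)/(n + 1).
- Expected score with T0 at fixed n: (n·p + p0)/(n + 1), where p is the post-baseline rate and p0 the rate at T0.
- Randomisation makes p0 equal in expectation across arms, so the between-arm difference is n/(n + 1) × (pA − pB).

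| n | factor | loss |
|---|---|---|
| 1 | 1/2 | 50% |
| 2 | 2/3 | 33% |
| 4 | 4/5 | 20% |
| 10 | 10/11 | 9% |

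With n uniform on 2 to 10 (assumption), the mean loss is (1/3 + 1/4 + … + 1/11)/9 = 1.520/9, about 17%.

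**Step 2: dependence on stay.** Take three patients with T0 not good and half their post-baseline nights good. One good night of 2 scores 1/3 = 33%, two of 4 score 2/5 = 40%, and five of 10 score 5/11 = 45%. Without T0 all three score 50%.

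In expectation the score is p − (p − p0)/(n + 1). With p = 0.29 and p0 = 0.09 (assumptions), n = 4 gives 0.29 − 0.20/5 = 0.25 and n = 3 gives 0.29 − 0.20/4 = 0.24. One night less in hospital costs 1 percentage point with identical sleep.

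**Step 3: simulation A.** Assumptions: two arms of 210; n = 2 + Poisson(2.5), capped at 10 (mean about 4.5); T0 good in about 9%; about 29% good nights on placebo; within-patient correlation 0.35, T0 included.

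| | T0 counted | T0 excluded | T0 excluded, T0 rating as covariate |
|---|---|---|---|
| Estimated difference, points | 6.6 | 8.2 | 8.3 |
| Power | 73% | 79% | 86% |

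With no effect on sleep, but one arm leaving about 1.0 to 1.5 nights earlier, counting T0 gives a false difference of about 0.8 to 1.4 points and a type I error of about 6–9%. With T0 excluded the bias is about nil and the error about 4–5%. One run of 1,500 trials gave 6.3% at 1.5 nights with T0 excluded. At 1.0 night the excess is hard to separate from simulation error: the standard error at 1,500 trials is √(0.05 × 0.95/1500) = 0.56 points, and one such run gave 5.8%.

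**Step 4: simulation B.** Assumptions: 40% against 50% good nights, 210 per arm, intraclass correlation 0.3, T0 drawn independently of later nights, 1,500 trials per cell. Power is shown without T0 → with T0.

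| n | no T0 good | 10% T0 good | 20% T0 good |
|---|---|---|---|
| 2 | 70.1 → 70.1% | 72.3 → 67.4% | 71.6 → 61.1% |
| 3 | 80.3 → 80.3% | 81.8 → 79.6% | 81.5 → 74.8% |
| 5 | 87.3 → 87.3% | 87.6 → 86.9% | 86.9 → 85.4% |
| 10 | 91.3 → 91.3% | 92.5 → 91.9% | 93.2 → 92.4% |

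In the first column every score is rescaled by the same n/(n + 1), so the test statistic does not change. Shrinkage of the estimate is therefore not the same thing as loss of power.

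**The case against.** The strongest reply is that the protocol never puts T0 in the denominator. The T0–T10 bracket belongs to the item on wearing the watch. The good-nights item has no time points, and the analysis sentence has no denominator. The primary outcome uses the same span under another name, "change in self-reported sleep quality during the treatment period (T0–T10", which suggests that T0–T10 marks the measurement schedule rather than the set of nights to be scored. Dosing also begins at once: "Study medication will be administered orally starting on the day of study enrolment". The night before the first dose therefore normally precedes enrolment, and on an ordinary reading the first night of the study period is the first treated one. Finally, the denominator of a secondary outcome and the covariates of its regression are commonly left to an analysis plan.

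Much of this stands. A reader might infer that the protocol defines this outcome over T0–T10 and that the treatment difference is in fact shrunk by 9–33%. The document does not support that: it is one literal reading of a phrase, and the percentages hold only if T0 is counted. Nor can one say that the T0 rating is unused as a covariate, because no covariates are listed for this regression.

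What does not fall away is that the article does state a window, attaches T0 to the same phrase, and collects the rating at T0. An analyst who follows the text would have grounds to count the untreated night, and nothing in it rules that out.

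**Conclusion.** The window is badly fixed and should be corrected. Counting T0 is a possible reading, not a stated rule. If it is followed, the loss in the estimated difference is exactly 1/(n + 1), and the score varies with length of stay even when sleep after baseline is the same.

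The consequence for power is modest and depends on assumed rates and stays. It runs from nothing (fixed n, no good baseline nights) to about 6 points in simulation A, and about 10 points only at n = 2 with 20% of baseline nights good. The type I error effect needs an assumed difference in stay between arms and is clear only near 1.5 nights. The gain from 79% to 86% comes from covariate adjustment, which is an improvement in precision rather than the repair of an error.

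The point is minor to moderate and confined to one secondary outcome. The primary analysis and the sample size are not touched.

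**What to change.** In Objectives, Secondary outcomes and Data analysis, use one definition: the proportion of good nights (rating 7 or above) among rated nights from T1 to T10 or discharge, where T1 rates the night after the first capsule. State that T0 is excluded from numerator and denominator. Use the word proportion in all three places. Enter the T0 numeric rating as a covariate in the regression for this outcome.

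The cost is one sentence. No new data are needed, because the rating is already taken at baseline and daily. The night dropped from the proportion carries no information on treatment, and its rating is put to use as the covariate.

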## Methods

### Trial design

This study is a multicentre, randomised, placebo-controlled trial. Figure 1 shows the trial design summary. This study will be conducted in two university teaching hospitals and in two teaching hospitals in the Netherlands: the Academic Medical Centre (AMC) Amsterdam, the University Medical Centre Groningen (UMCG), Gelre Hospitals Apeldoorn and the Medical Centre Leeuwarden (MCL). The design of this trial protocol has followed the recommendations of the SPIRIT 2013 statement.^33^

